#### Intervention Group

After the inclusion, the first part of the intervention (group session) will be carried out in each health center and the intervention group will receive appointments for:

Visit 1: It will take place 3 months after the intervention. It will involve the measure of adherence and other variable changes, encouragement about inhalation techniques and motivational aspects related to treatment adherence.

Visit 2: It will take place 6 months after the intervention. It will involve the measure of adherence, other variable changes and encouragement about inhalation techniques and motivational aspects related to treatment adherence.

Visit 3: It will take place after 1 year follow-up. All the study data will be recorded and encouragement about inhalation techniques and motivational aspects related to treatment adherence.

There was a pre-adherence visit prior to all visits as explained previously.

Adherence will be measured at each visit to control its evolution during the follow-up period. All individual follow-up visits will be videotaped to identify the motivational aspects and skills which each patient needs to be applied at the next visit.

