##### Group session

the session will last 2 hours including the patient's reception, the material distribution, the intervention and the farewell. The intervention is structured in three parts: the first part will be conducted following the focus group methodology. The number of patients will be about 6 to 9 per group. In the second part, patients will receive information about their disease and treatment with the aid of the distributed material. The third part will be conducted as a training session about inhalation technique.

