### Follow up

#### Control Group

they will be appointed for:

Visit 1: It will take place 3 months after the inclusion. It will involve the measure of adherence and other variable changes.

Visit 2: It will take place 6 months after the inclusion. It will involve the measure of adherence and other variable changes.

Visit 3: It will take place after 1 year follow up. All the study data will be recorded including treatment adherence.

There will be a pre-adherence visit before each follow-up visit except for the inclusion one. The reason for the pre-adherence visit is to ask the patient to bring a new container that will be marked with the date in which it is opened in order to count doses/pills through the month. This is done because most of the devices that patients use last 30 days. The pre-adherence visit will be done by telephone to guarantee the follow-up.

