### Statistical Analysis

A descriptive statistical analysis will be performed for all the study variables. We will calculate the mean, median and standard deviations for quantitative variables, and the absolute and relative frequency for qualitative variables.

The 95% confidence level will be applied. The analysis will be made under an intention-to-treat procedure. The between-group comparison for the primary outcome will be explored using the Chi Square Test. The Relative Risk Reduction (RRR), the Absolute Risk Reduction (ARR) and the Number Needed to treat (NNT) will be calculated. Inferences for the secondary outcomes will be made using an analysis of variance (ANOVA). Finally a logistic regression model will be performed for the primary outcome [treatment adherence (yes/not)], considering the intervention as the predictive variable and the rest of the independent measures as the possible modifying factors. We will use the usual 5% significance level (α = 0.05) and the SPSS statistical package, version 15.0, to run the proposed analysis.

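### Visits 1 and 2 are dated from inclusion in the control arm but from the later group session in the intervention arm, and the start of the year leading to Visit 3 is ambiguous

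*Protocol article*

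**What the plan says.** The Recruitment section places random allocation at the inclusion visit, with baseline adherence measured afterwards in both arms. Inclusion and randomization are therefore the same time point.

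For controls, the Follow up section gives "Visit 1: It will take place 3 months after the inclusion", "Visit 2: It will take place 6 months after the inclusion" and "Visit 3: It will take place after 1 year follow up".

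For the intervention arm it gives "Visit 1: It will take place 3 months after the intervention", "Visit 2: It will take place 6 months after the intervention" and "Visit 3: It will take place after 1 year follow-up". The same section says that the first part of the intervention, the group session, is held in each health centre once patients have been included. On session size, the Group session section says: "The number of patients will be about 6 to 9 per group".

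The Background section times these assessments in two ways. The main objective refers to one year of follow-up and ties only the 3- and 6-month reinforcement visits to the intervention. The first specific aim, written for both groups, counts the 3-month, 6-month and one-year measurements all from the intervention.

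The Statistical Analysis section says: "The analysis will be made under an intention-to-treat procedure".

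**The concern.** Randomization makes the arms comparable from the moment of allocation. If outcome visits are dated from allocation in one arm and from a later event in the other, the arms are assessed at different times since randomization. They may also differ in season, and intervention patients have d months longer in which to drop out or have their prescription changed before the same nominal visit.

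The later event is also one that only intervention patients can experience, and some may not. A patient allocated to the intervention who never attends a session has nothing from which to count Visits 1 and 2, while every control does. Intention-to-treat analysis needs outcome data on everyone as randomized, so a schedule that leaves some patients in one arm undated works against it. The Study limitations section itself names missing data as the main threat.

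**Working it through.** **Inputs.** Allocation at inclusion, 1:1 in blocks of 4, six centres (Recruitment); 140 patients sampled consecutively (Participants, Sample size); sessions of about 6 to 9 (Group session); visit timing (Follow up; aims in Background). The article gives neither the accrual period nor the time from inclusion to session.

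**Step 1: time since randomization at each visit.** Let d be the months from inclusion to session.

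| Visit | Control | Intervention | Difference |
|---|---|---|---|
| 1 | 3 | 3 + d | d |
| 2 | 6 | 6 + d | d |
| 3, year counted from inclusion | 12 | 12 | 0 |
| 3, year counted from the session (intervention arm only) | 12 | 12 + d | d |

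The first two rows follow directly from the text. The last two are alternative readings. If the year runs from inclusion, the specific aim is contradicted and the interval from Visit 2 to Visit 3 in the intervention arm becomes 12 - (6 + d) = 6 - d months, against 6 in controls. If it runs from the session, the arms differ by d and controls still have no matching start point.

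**Step 2: could d be close to zero?** About 140/2 = 70 intervention patients over 6 centres is 70/6 = 11.7 per centre. One session of 6 to 9 therefore takes 6/11.7 = 51% to 9/11.7 = 77% of a centre's intervention patients. With even accrual over T months (assumed) and a session held as soon as g patients are available, the rate per centre is 11.7/T per month. The first patient then waits (g - 1)/rate and the average patient half of that.

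| Accrual T (assumed) | Rate per centre per month | Mean d, g = 6 to 9 | First patient's wait |
|---|---|---|---|
| 6 months | 1.94 | 1.3 to 2.1 months | 2.6 to 4.1 months |
| 12 months | 0.97 | 2.6 to 4.1 months | 5.1 to 8.2 months |
| 24 months | 0.49 | 5.1 to 8.2 months | 10.3 to 16.5 months |

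These figures are illustrations. If a centre includes its patients in a batch and holds the session promptly, d is near 0.

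**Step 3: patients without a session.** If 5%, 10% or 20% of the 70 never attend (assumed), 70 × 0.05 = 3.5, 70 × 0.10 = 7 or 70 × 0.20 = 14 intervention patients have no date for Visits 1 and 2. In the control arm the number is 0.

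**Step 4: direction.** The only time trend in the article is in the Background: self-reported adherence to inhaled treatment of 60% at one year and 50% at five years in a cited study. Taken as linear, that is 10/48 = 0.21 points per month, or about 0.6 points for an assumed d of 3 months, against a target difference of 25 points. On that trend, later assessment of the intervention arm would slightly reduce the apparent effect. Loss of less adherent non-attenders would act the other way, but the article has no data on them.

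**Sample size.** The stated 140 does not depend on visit timing, so a common clock leaves it unchanged.

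**The case against.** The strongest reply has four parts.

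- **Visit 3 has the same wording in both arms.** The main objective is set at one year, and on the plain wording of Follow up every patient, including one who missed the session, can be given a date one year from inclusion. This stands. A reader might infer that the arms are misaligned at every assessment, that non-attenders have no visit dates at all, or that the one-year outcome falls at month 15 in one arm and month 12 in the other. The article does not support this. The month-15 figure needs both a Visit 3 counted from the session and a 3-month wait, and Follow up states neither.
- **The delay may be short.** Patients are telephoned from existing records and given appointments, so inclusions could be batched. This stands as far as the size of d goes, but nothing in the article requires batching or limits the delay.
- **Non-attenders are covered.** The plan declares intention-to-treat, offers three phone calls and three rescue appointments, and refers to a researcher manual that may hold more detail. This stands in part. A reader might infer that non-attenders drop out of one arm and inflate the effect; that is speculation. But a rescue appointment rebooks a visit that already has a date and does not create one. The two start points are stated text, not detail left to a manual.
- **Dating from the session fixes the time since intervention.** That suits a reinforcement visit, and it is a real advantage, but it does not give a comparison at equal time since randomization.

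**Conclusion.** The point holds for Visits 1 and 2: as written, the arms are assessed d months apart in time since randomization, and intervention patients who never attend a session have no defined date for either visit. For Visit 3, the assessment that serves the main objective, the start point is ambiguous between the specific aims and Follow up; it is not shown to differ between arms.

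The size is d, which cannot be derived from the article. It ranges from near 0 with prompt sessions to a mean of 1.3 to 4.1 months if accrual takes 6 to 12 months, assuming even accrual and sessions filled within each centre. The direction of any bias is not established either. This is an avoidable asymmetry between arms that can be removed cheaply; it is not evidence that the trial's result would be distorted in a known direction.

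**What to change.** Date the outcome assessments at Visits 1, 2 and 3 from randomization in both arms, with the same visit windows. Bring the specific aims and the two Follow up schedules into line with that rule, so that no control time point is counted from the intervention. State that intervention patients who miss the group session are assessed on the same dates and analysed as randomized.

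This changes the wording of the schedule and leaves the sample size as it is. The cost is that some intervention patients will be assessed less than 3, 6 or 12 months after their session. Recording the session date for each patient would allow that interval to be described. Delaying randomization until a full session can be formed is a larger procedural change and is not needed for this purpose.

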### Statistical Analysis

A descriptive statistical analysis will be performed for all the study variables. We will calculate the mean, median and standard deviations for quantitative variables, and the absolute and relative frequency for qualitative variables.

The 95% confidence level will be applied. The analysis will be made under an intention-to-treat procedure. The between-group comparison for the primary outcome will be explored using the Chi Square Test. The Relative Risk Reduction (RRR), the Absolute Risk Reduction (ARR) and the Number Needed to treat (NNT) will be calculated. Inferences for the secondary outcomes will be made using an analysis of variance (ANOVA). Finally a logistic regression model will be performed for the primary outcome [treatment adherence (yes/not)], considering the intervention as the predictive variable and the rest of the independent measures as the possible modifying factors. We will use the usual 5% significance level (α = 0.05) and the SPSS statistical package, version 15.0, to run the proposed analysis.

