### Sample size

it was calculated to detect an adherence percentage difference between the two groups of 25%, with a statistical power of 80% and a confidence level of 95%, assuming a percentage of expected losses of 15%. The final sample size was 140 patients with COPD that meet the selection criteria mentioned above.

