### Study limitations

The main study limitation is the selection bias due to the missing data. In order to diminish this bias, we will apply several strategies:

- An increase of 15% in the sample size (expected losses)

- Three phone calls at different days and times for unreachable patients

- Rescue appointments for the non-assistants to visits (three different appointments)

Other aspect is the Hawthorne effect along the study (ie, tendency of subjects participating in a research study to change their behaviour). Although this could affect overall estimates the adherence, the implications might be less important in comparing results of different measurements tools (unless, of course, the effect is differentially captured by each measurement tool); furthermore, it is difficult to perceive that any potential Hawthorne effect would be maintained over the many months of study.

In addition we take into account the possible contamination between the control and the intervention group because of the relationship between subjects in their daily life (neighborhood, relatives, social networks or associations). However, in another educational intervention study performed with obese patients in our area we did not find a significant level of this effect [35]. We also believe that the intervention characteristics (several steps, small groups and individual visits) that we have described will have little influence on contamination between groups.

Another important aspect to consider is the protocol and the intervention standardization. This is why the dynamic has been structured in an exhaustive way and the intervention will be performed by two professionals trained in communication, disease knowledge and inhalation techniques of the different devices used by COPD patients. Furthermore, we have designed a manual for the researchers where we explain the working plan, the different parts of intervention (the group session and the individual visits), the protocol scheme to know what they have to measure each time and the details to asses each variable included in the study. In this way, the procedure can be replicated elsewhere.

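### The chi-square test and N = 140 treat all patients as independent, but only intervention patients share group sessions; if outcomes correlate within sessions, the standard error is too small and the 80% power does not hold under a valid analysis

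*Protocol article*

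**What the plan says.** **Allocation (Protocol article, Recruitment).** Patients are randomised individually, 1:1, in blocks of four, across six health centres, with both arms present in each centre.

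**Delivery (Group session; Follow up).** Intervention patients attend one two-hour session held in their health centre: "The number of patients will be about 6 to 9 per group". Control patients attend measurement visits only.

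**Link to later visits (Motivational Aspects; Skills Training).** The session is run as a focus group, chosen because it brings out interaction between members. Inhaler technique is demonstrated and discussed in front of the group. The team reviews each session's video and agrees a motivational strategy for the individual visits.

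**Staff (Study limitations).** The article states that "the intervention will be performed by two professionals trained in communication" and in other relevant skills.

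**Sample size.** The size was set "to detect an adherence percentage difference between the two groups of 25" percent, "with a statistical power of 80% and a confidence level of 95" percent, "assuming a percentage of expected losses of 15" percent. The result is 140 patients. No ICC or design effect is mentioned.

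**Analysis (Statistical Analysis).** "The between-group comparison for the primary outcome will be explored using the Chi Square Test". A logistic model follows, with the intervention as predictor and patient-level covariates. Neither analysis has a term for session group. "We will use the usual 5% significance level" is the stated threshold.

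**The concern.** Patients who sit in the same session share its discussion, its training and a strategy that starts from it. Their one-year adherence may therefore be more alike than that of patients from different sessions. This can happen in the intervention arm only, because controls have no session.

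The chi-square test gives each intervention patient full weight as independent information. With positive within-session correlation, the intervention proportion varies more than the binomial formula allows, and the test uses too small a standard error. Two things are then at stake. The primary p-value and the interval around the ARR may be too favourable. The stated power would also belong to a test that does not hold its level, and a valid test on the same 140 patients would have less.

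**Working it through.** **1. Inputs from the document**
- Difference 25 percentage points, power 80%, alpha 0.05 (two-sided assumed), losses 15%, N = 140, so 70 per arm.
- Completers: 140 × 0.85 = 119, or 59.5 per arm.
- Session size 6 to 9, so 70/9 = 7.8 to 70/6 = 11.7, i.e. about 8 to 12 sessions.

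**2. Assumptions, because the document gives no figure**
- Adherence 40% (control) versus 65% (intervention).
- ICC 0.01, 0.05 or 0.10.
- Mean session size 7.5 at the start. Completers per session: 7.5 × 0.85 ≈ 6.4. The loss is applied to session size as well as to arm size, so that the two agree.

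**3. Reproducing N = 140**

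The usual two-proportion formula (pooled variance under the null, independent patients), divided by 0.85 for losses, gives:

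| Control rate | n per arm | Total N |
|---|---|---|
| 25% or 50% | 58 | 138 |
| 30% or 45% | 61 | 144 |
| 35% or 40% | 62 | 146 |

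So 140 is consistent with independent patients and no design effect. With 59 completers per arm, the same formula gives power of 78% to 81% for control rates of 25% to 50%. There is no reserve to absorb clustering.

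**4. Formulas for the partially nested design**
- Design effect, intervention arm only: DE = 1 + (6.4 − 1) × ICC.
- Type I error of the unadjusted test when the average effect is zero: 2 × [1 − Φ(1.96 / √((1 + DE)/2))].
- Power of a cluster-adjusted test: Φ(0.25 / SE − 1.96), with SE = √(0.40 × 0.60/59.5 + 0.65 × 0.35 × DE/59.5) = √((0.24 + 0.2275 × DE)/59.5).

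**5. Results**

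| ICC | DE | Type I error | SE | Power, adjusted test |
|---|---|---|---|---|
| 0 | 1.000 | 5.0% | 0.0886 | 80.5% |
| 0.01 | 1.054 | 5.3% | 0.0898 | 79.5% |
| 0.05 | 1.270 | 6.6% | 0.0943 | 75.5% |
| 0.10 | 1.540 | 8.2% | 0.0996 | 70.9% |

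Worked line for ICC 0.05: DE = 1 + 5.4 × 0.05 = 1.27. √(2.27/2) = 1.065 and 1.96/1.065 = 1.840, so the two-sided error is 6.6%. SE = √((0.24 + 0.2889)/59.5) = 0.0943, 0.25/0.0943 = 2.65, and Φ(2.65 − 1.96) ≈ 0.755.

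**6. Checks**
- A beta-binomial simulation of the chi-square test with groups of 6 at ICC 0.05 gave 6.6% to 7.1%, against 5.1% to 5.6% at ICC 0. This agrees with the formula.
- Taking 6 and 9 as the extremes of session size with no shrinkage gives type I error of 6.5% to 7.4% at ICC 0.05 and 8.0% to 9.8% at 0.10.
- The power figures use the normal quantile 1.96. A small-sample correction for 8 to 12 clusters would lower them somewhat further.

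**The case against.** **The inflation is not certain.** Under individual randomisation, if the intervention changes no patient's outcome, attending a session cannot create correlation. The test then keeps about its nominal level: a simulation of this sharp null with 119 patients, six centres and a centre ICC of 0.10 rejected in 4.7% of runs. This objection stands. The type I figures apply to a zero average effect that varies between session groups, and a reader who infers that the p-values must be too small goes beyond the document.

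**The ICC may be small.** There is only one group session. The later visits are individual and tailored to the patient, the content is standardised by a manual, and the outcome is read at one year. All of this could dilute a group effect, and at ICC 0.01 nothing of practical weight changes. It does not show that the ICC is zero, because the session is meant to be interactive and its findings are carried into the visits.

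**The two professionals and the centres.** A reader might blame the small number of providers. If the same pair runs every session, their effect is common to the whole arm. It adds no variation between groups, and a session-cluster analysis cannot remove it. The article does not say that the individual visits are divided between them. Centre correlation is shared by both arms and does not by itself make p-values too small.

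**The planned test loses little power.** This is correct. The unadjusted chi-square loses about 1 to 4 points up to ICC 0.10. The larger loss appears only once the test is made valid.

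**A condensed article leaves detail to the full plan.** This does not answer the point, because the primary test and N are both fixed in this text and both assume independence.

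**A mixed logistic model may be unstable with 8 to 12 small clusters, and it does not yield the planned ARR and NNT.** This stands, and it determines the form of the fix.

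**Conclusion.** The point holds in conditional form. The design is partially nested, and the test, the model and the sample size ignore that. If outcomes correlate within session groups, for example because the intervention works better in some groups than in others, the standard error of the arm difference is understated and 80% power is not available under a valid analysis.

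How much this matters depends on an ICC that the document does not give. Near 0.01 it can be ignored. From about 0.05 it is material: roughly 6.6% instead of 5% type I error for a zero average effect, and 76% instead of 80.5% power. At 0.10 the figures are about 8.2% and 71%. They also rest on the assumed 40% versus 65% adherence and about 6.4 completers per session. The design defect is clear from the text; the size of its effect is not. The change is worth making before analysis.

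**What to change.** - Record the session group of every intervention patient.
- Make the primary analysis a risk difference with cluster-robust, small-sample-corrected standard errors, with session groups as clusters in the intervention arm and each control as a singleton. ARR and NNT then keep their planned meaning.
- Use a partially nested mixed logistic model as a sensitivity analysis only, and keep the chi-square test as descriptive.
- Report the estimated ICC, and restate power over a range of ICC values without changing N.

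The cost is a change of analysis wording and one extra data item that is known when sessions are scheduled. Randomisation, visits and sample size are untouched. The downside is wider confidence intervals, few effective degrees of freedom with about 8 to 12 clusters, and a less favourable stated power. If the ICC proves close to zero, only the small loss from the degrees-of-freedom correction remains.

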Between 1998 and 2003 our research team carried out a cohort study of patients with COPD in two health centers in Malaga. The Batalla Test [19], the Morinsky-Green test [20] and the self-reported compliance from Haynes and Sackett test [21] were all included as treatment adherence evaluation methods. We found little consistent data. Between 2004 and 2006, we performed another cohort study in 195 COPD patients from 4 health centers. Patients have been followed up during 1 year and we have used four therapeutic adherence measures: the Batalla test, the Morinsky-Green test, the Haynes-Sackett test and the dose/pill count. In this study we selected the dose/pill count as the reference method to measure adherence and we calculated the diagnostic validity of the self-reported methods. We found that the use of the Batalla test and the Morisky-Green test together was the most reliable way to assess adherence by self-reported methods and we proposed a strategy to measure adherence in clinical practice depending on the adherence prevalence [22]. Taking all this into account, our next step in the study of adherence was the design of a multifactor intervention to improve treatment adherence in patients with COPD.

The main objective of this study is to evaluate the effectiveness of a multifactor intervention (COPD information, dose reminders, audiovisual material, motivational aspects and inhalation techniques training) to improve the therapeutic adherence in COPD patients with inhaled scheduled treatment after one year follow-up with two reinforcement visits (3 and 6 month after intervention). The second objective is to describe the main factors related to adherence. The specific aims are:

- To evaluate in two study groups treatment adherence prevalence with inhaled medication (primary outcome variable) at the beginning of the study, at three and six months and at one year after the intervention.

- To evaluate the functional status using a forced spirometry and the quality of life (St George Respiratory questionnarie, EuroQoL-5D) and the clinical progress (SeguiEPOC) as secondary outcome measures in both groups.

- To analyse the main factors related to therapeutic adherence.

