#### Secondary outcome

functional status (spirometry), quality of life (St George respiratory questionnaire [27], and EuroQoL-5 D [28]) and the clinical progress with SeguiEPOC questionnaire.

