#### Independent variables

age, sex, educational level, comorbidity, smoking history, COPD severity grade (according to SEPAR guidelines [29]), prescribed medication, family support (Family Apgar Test [30]): social support (DUKE-UNC Test [31]).

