### Recruitment

Patients will be contacted using their health center records. They will be invited to participate in the study after a brief explanation by telephone about the research aims and they will receive an appointment in the health center. At this first appointment (inclusion visit) patients will receive more detailed information about the study and if they agree to participate, they will sign the written consent.

At this point, subjects will be divided randomly into two groups using the block randomization technique. The blocks consist of 4 patients, two subjects per group [Intervention (I) and control (C)]: (IICC); (CCII); (CICI); (ICIC); (ICCI); (CIIC). Consequently, the numbers in the two groups never differ at any time by more than two. The blocks will be marked with a number from 1 to 6 and we will choose blocks at random to create the allocation sequence using a sequence of random numbers generated by Microsoft Excel 2003 program with the function fx:RAND(). We will need 35 random blocks; and the final list of the included patients in each arm of the trial will be set in advance. The researcher who will allocate the patient will have the open-list of randomization, but there will be no change of patient group related with the subjects characteristics. Because the patients are from 6 health centers, the randomization and the presence of the intervention and control subjects in all the health centers will be guaranteed.

After randomization all the study data will be recorded and the adherence will be measured in both groups.

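### Baseline values are collected, but no baseline term is named for the secondary-outcome ANOVA or the adherence model; adjusting would gain efficiency at almost no cost

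*Protocol article*

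**What the plan says.** **Secondary outcomes.** The Secondary outcome section names "functional status (spirometry), quality of life (St George respiratory questionnaire" and EuroQoL-5D) and the SeguiEPOC questionnaire. The Statistical Analysis section gives their method in one sentence: "Inferences for the secondary outcomes will be made using an analysis of variance (ANOVA"). It does not say whether follow-up values, changes from baseline or repeated measures are analysed, and it names no covariate.

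**Adherence.** The main test is unadjusted: "The between-group comparison for the primary outcome will be explored using the Chi Square Test". A logistic model follows, "considering the intervention as the predictive variable and the rest of the independent measures as the possible modifying factors". The Independent variables section lists nine such measures. It begins "age, sex, educational level, comorbidity, smoking history, COPD severity grade" and goes on to prescribed medication, family support and social support. Baseline adherence is not among them.

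**What is measured at the start.** The Recruitment section says: "After randomization all the study data will be recorded and the adherence will be measured in both groups". The specific aims in the Background give the times for adherence as "at the beginning of the study, at three and six months and at one year after the intervention". For the dose/pill count, the Control Group section adds a restriction: "There will be a pre-adherence visit before each follow-up visit except for the inclusion one".

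**The concern.** The trial measures these outcomes at inclusion and again during follow-up, but the stated analyses do not say that the first measurement enters any between-group comparison. If it does not, stable differences between patients stay in the error term and a chance imbalance at baseline passes into the estimated effect. The Sample size section bases the 140 patients on adherence alone, so the secondary outcomes have no planned power of their own, and an avoidable loss of efficiency falls directly on them. For adherence, the patient's own baseline status is a natural predictor of later adherence, yet the model intended to examine factors related to adherence leaves it out.

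**Working it through.** **The plan's own figure.** The sample size is 140 for a 25-point difference, 80% power, 95% confidence and 15% losses. The control rate used is not stated. With a two-sided 5% test and no continuity correction:
- 25% v 50%: 58 per arm; 58/0.85 rounds up to 69, total 138.
- 30% v 55%: 61 per arm; 61/0.85 rounds up to 72, total 144.

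So 140 is reproduced to within a few patients and is not in dispute. After 15% loss, 140 × 0.85 = 119 remain, or 59.5 per arm.

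**Secondary outcomes.** Let r be the correlation between the baseline and one-year values. It is not in the documents, so a range is assumed. With equal SD at both times, set to 1, the variance that enters the comparison is:
- follow-up values only: 1
- change scores: 2(1 − r)
- ANCOVA on baseline: 1 − r²

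The ratio of ANCOVA to change scores is (1 − r²)/[2(1 − r)] = (1 + r)/2. A two-time-point repeated-measures ANOVA tested through the group-by-time term is the change-score case.

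Take the effect that gives 80% power with follow-up values only: √(2/59.5) × (1.960 + 0.842) = 0.514 SD. For residual variance v, power is Φ(2.802/√v − 1.960).

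| | r = 0.3 | r = 0.5 | r = 0.7 |
|---|---|---|---|
| ANCOVA variance, 1 − r² | 0.91 | 0.75 | 0.51 |
| Reduction v follow-up only | 9% | 25% | 49% |
| Equivalent N, 119/(1 − r²) | 131 | 159 | 233 |
| Change-score variance, 2(1 − r) | 1.40 | 1.00 | 0.60 |
| ANCOVA/change ratio, (1 + r)/2 | 0.65 | 0.75 | 0.85 |
| Reduction v change scores | 35% | 25% | 15% |
| Power, follow-up only | 80% | 80% | 80% |
| Power, change scores | 65.8% | 80.0% | 95.1% |
| Power, ANCOVA | 83.6% | 89.9% | 97.5% |

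In this large-sample calculation ANCOVA has the smallest variance in every column. How much it gains depends on which ANOVA was meant.

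**Adherence.** Trials were simulated (3,000 per setting, 60 per arm, 40% v 65% adherent), comparing the unadjusted chi-square test with the likelihood-ratio test for arm in a logistic model that also contains baseline adherence. The correlation is between binary baseline and follow-up adherence in the control arm.

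| Correlation | Unadjusted power | Power with baseline |
|---|---|---|
| 0.19 | 0.81 | 0.81 |
| 0.33 | 0.81 | 0.84 |
| 0.49 | 0.80 | 0.88 |
| 0.64 | 0.80 | 0.94 |

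Simulation error is about √(0.8 × 0.2/3000) = 0.007. There is no gain at weak correlation and a useful one at moderate to strong correlation.

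**The case against.** **The ANOVA may already use baseline.** One sentence does not show that baseline is thrown away. The follow-up sections speak of recording changes in the other variables, so a change-score or repeated-measures analysis is a live reading, and a condensed article may leave model terms to a fuller plan. This stands in part. A reader might infer that the baseline values are discarded; the text does not establish that. What remains is that the article names a method and a covariate list, neither includes a baseline outcome value, and ANCOVA is more efficient under either reading.

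**The gain may be small.** This also stands in part. Quoting only the comparison with follow-up values at high correlation would overstate it. At r = 0.7 the saving is 49% against follow-up values but 15% against change scores, and at r = 0.3 it is only 9% against follow-up values.

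**Adherence is different.** This stands. In logistic regression a prognostic covariate does not shrink the standard error of the conditional log odds ratio; it can raise power. The main adherence comparison is in any case the chi-square test, and the logistic model serves largely to explore related factors.

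**A baseline dose count may not exist.** This stands as a limit. The Control Group section excludes a container-marking contact before inclusion, while the Intervention Group section, referring back to that account, speaks of one before all visits.

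**The unadjusted comparisons are valid.** Agreed. A reader might infer bias from the missing baseline term, but randomisation protects against that.

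**Conclusion.** The point holds as an efficiency improvement, not as an error that threatens validity. The article names ANOVA for the secondary outcomes without a baseline term, and its adherence covariates omit baseline adherence, although both are said to be measured at inclusion. For assumed r = 0.3/0.5/0.7, ANCOVA would reduce variance by 9%/25%/49% against follow-up-only ANOVA and by 35%/25%/15% against change scores. These figures assume equal SDs at the two times, a common correlation in both arms and about 119 evaluable patients. For adherence, the gain is in power and depends on a reasonably strong correlation between baseline and later adherence. The documents do not support stronger conclusions: that baseline data are certainly discarded, that the comparisons are biased, or that a particular multiple of the sample size is being lost.

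**What to change.** - State that each continuous secondary outcome is compared at one year by ANCOVA with arm and its own baseline value, or by a linear mixed model with baseline as covariate where several visits are recorded.
- Add baseline adherence by the Morisky-Green or Batalla test to the logistic model. The chi-square comparison can stay as it is.
- Use a baseline dose/pill count only if the Control Group and Intervention Group sections are reconciled and show that one is obtained.

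The cost is a change of analysis wording and a little more analysis work, with no new data.

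A separate, optional change would be to record the baselines before allocation is revealed. The Recruitment section places them after randomisation from an open list, so self-reported baselines could be given with the allocation known. That alters the order of the inclusion visit and so goes beyond a change of wording.
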